
#### Safety related outcome

3.4.2

The primary safety outcome will be the occurrence of adverse events and serious adverse events during the study. Any unfavourable change in health, or the onset or worsening of an undesirable sign, symptom or medical condition after enrolment, will be recorded as an adverse event (AE), irrespective of whether it is considered related to the intervention. All AEs will subsequently be classified according to severity and their relationship to the device and/or procedure.

A serious adverse event (SAE) will be defined as any untoward medical occurrence, whether or not considered related to the investigational intervention, that results in death, is life-threatening, requires hospitalisation or prolongation of existing hospitalisation, results in persistent or significant disability or incapacity, constitutes a congenital anomaly or birth defect, requires intervention to prevent permanent impairment or damage, or is considered an important medical event. Hospitalisations related to elective or previously planned procedures for pre-existing conditions that have not worsened after study enrolment will not be considered SAEs.

SAEs will be reported to the sponsor and handled in accordance with applicable national legislation and local ethics committee requirements. The investigator will be responsible for assessing and reporting safety events throughout the study. Both AEs and SAEs must be reported to the sponsor and principal investigator in a timely manner according to local requirements.

#### Feasibility related outcome

3.4.3

Feasibility will be assessed by determining the proportion of patients with a successful DTM SCS trial. Technical feasibility will be evaluated by documenting technical issues related to DTM SCS, battery consumption and recharge frequency. Programming information will be collected for the different stimulation groups, including the percentage use of each group. Clinically effective stimulation parameters, including frequency, pulse width and amplitude, will be identified at each post-implantation visit.

Additional technical information will be obtained from the IPG. For patients treated with closed-loop DTM SCS, in-clinic ECAP streams will be collected to evaluate ECAP signal stability through JSON files. At-home SCS device use, programming and IPG battery performance will be obtained from Medtronic data reports and analysed as part of the feasibility evaluation.

The overall study flow is shown in Figure 1. If a patient does not attend a scheduled outpatient follow-up visit, the study team will attempt to contact the patient by telephone. When the patient agrees, any assessments that can be completed remotely will be collected by phone.

**Figure 1 F1:**
[figure not shown]
Patient flow chart. Overview of screening, recruitment, baseline assessment, SCS trial, IPG implantation and follow-up visits at 1, 6 and 12 months after IPG activation with the set of outcome measures.

### Patient and public involvement

3.5

The selection of questionnaires was informed by previous work identifying treatment goals in patients before SCS implantation through qualitative interviews with independent researchers (39), as well as by studies exploring outcomes that patients with chronic pain aim to achieve (40). In addition, experience gained during the previous DETECT study was used to refine the assessment battery for ENDLESS (16). Questionnaires that were perceived as difficult or burdensome by patients were reconsidered, and the outcome set was adapted where possible to improve feasibility and acceptability while maintaining clinically relevant assessment domains. Patient support groups will be offered the opportunity to discuss the study findings after completion of the study. The results of ENDLESS may further support patient and public involvement by identifying outcomes and assessment methods that are meaningful and feasible for patients undergoing DTM SCS.

### Data management

3.6

Study data will be collected and managed using secure web-based data collection systems. Qualtrics will be used for patient-reported outcome measures. Patients will complete questionnaires by accessing a study-specific web link or by scanning a quick-response code that directs them to the relevant assessment. REDCap will be used as the electronic case report form for clinical, safety, feasibility and device-related data entered by the investigator or delegated study personnel.

Each participant will be identified by a unique study code consisting of the centre identification number and an individual patient number assigned by the investigator. Directly identifiable personal information will be stored separately from study data where possible, and analyses will be performed on pseudonymised datasets.

The following source data will be generated during the study: medical history obtained from the patient's medical file to assess eligibility; signed informed consent forms; questionnaire results; personal health-related study data; safety reports; SCS programming parameters and device-derived data, including comma-separated value files, JSON files and IPG session reports; and statistical analysis scripts in R and SAS-readable formats.

For EMA and Garmin data collection, the Labfront and m-Path platforms will be used. Data will be encrypted during transmission, and Labfront data will be archived using Amazon Web Services S3 Glacier. The m-Path system was developed according to privacy-by-design principles. Both platforms will be used in accordance with the European Union General Data Protection Regulation and applicable institutional data-protection requirements (41).

Source documents will be completed at the time of the participant's visit or as soon as possible thereafter. Participating sites will retain relevant source documents and centre-specific essential documents in the Investigator Site File. Study-related documents and trial data will be archived securely in accordance with International Council for Harmonisation Good Clinical Practice guidelines and applicable national regulations. Measures will be taken to prevent accidental loss, premature destruction or unauthorised access. Trial data will not be destroyed without the sponsor's agreement. Patient identification codes will be retained for at least 25 years after completion or discontinuation of the study. The investigator will allow study-related monitoring, audits, Ethics Committee review and regulatory inspections by providing direct access to relevant source data and documents.

### Data analysis

3.7

Data processing and statistical analyses will be performed on pseudonymised datasets after completion of follow-up, data monitoring and data cleaning. Analyses will be conducted by the project biostatistician using RStudio and SAS. Patient flow throughout the study will be presented in a flow diagram. Baseline demographic and clinical characteristics will be summarised descriptively for the total study population and, where relevant, by stimulation mode or other clinically meaningful subgroups.

Given the longitudinal design of ENDLESS, repeated measurements within patients will be accounted for in the statistical analyses. The primary outcome, pain intensity up to 12 months after IPG activation, will be analysed using longitudinal mixed models for the overall cohort. Repeated observations will be modelled within patients, and clustering of patients within recruiting centres will be accounted for, where supported by the data. Comparisons between open-loop and closed-loop DTM SCS will be considered exploratory and will account for relevant baseline characteristics and centre-level clustering. Where feasible, sensitivity analyses will be performed in centres that enrolled patients treated with both stimulation modes. If stimulation mode is completely or nearly completely confounded with recruiting centre, comparative results will be reported descriptively and will not be interpreted as evidence of causal comparative effectiveness.

Secondary outcomes will be analysed according to the type and distribution of the data. Longitudinal mixed models will be used for continuous repeated outcomes, generalized mixed models for categorical or non-normally distributed outcomes, and Tweedie generalized linear models when outcomes show a discrete mass at zero (42). Claims of statistical significance for secondary outcomes will only be made if a statistically significant effect is observed for the primary outcome. If the primary outcome is not statistically significant, analyses of secondary outcomes will be interpreted descriptively and exploratively. Main analyses will be performed using the data as observed. Sensitivity analyses will be conducted to assess the robustness of the findings in relation to the handling of missing data.

In addition to mixed-effect modelling, latent class trajectory modelling (LCTM) will be applied to explore patterns of response over time (43, 44). LCTM allows heterogeneous patient populations to be grouped into more homogeneous clusters based on an unobserved latent variable (45). Random effects can be incorporated to account for individual variation within these clusters (46). This data-driven approach will be used to identify trajectories of clinical response within the ENDLESS cohort, rather than assigning patients to predefined categories based only on baseline patient or clinical characteristics.

Patient-level quality-adjusted life-years (QALYs) will be calculated using EQ-5D-5L index scores. QALYs will be estimated using the area under the curve method, in which utility values are linearly interpolated over the study period and the resulting areas are summed (47). A second QALY estimate will be calculated by extrapolating the baseline EQ-5D-5L index value over 12 months, representing the expected QALY without additional treatment (34). Incremental QALYs will be calculated by subtracting the baseline-extrapolated QALY from the QALY observed during DTM SCS over the 12-month follow-up period.

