#### Effectiveness outcomes

3.4.1

The outcome measures are described below, while their timing and collection frequency are summarised in Table 1.

**Table 1 T1:** Overview of outcome measurements at each ENDLESS study visit.

Outcome domain	Outcome measurement	Measurement tool/source	Collection frequency/window	Baseline screening V0	1 month V1	6 months V2	12 months V3
Effectiveness	Current pain intensity	VAS through EMA	Three prompts daily for seven consecutive days at each assessment period	✓	✓	✓	✓
	Average pain intensity	NRS	Once per applicable assessment period	✓	✓	✓	✓
	Medication use	EMA	Three prompts daily for seven consecutive days at each assessment period	✓	✓	✓	✓
	Negative affect	EMA	Three prompts daily for seven consecutive days at each assessment period	✓	✓	✓	✓
	Disability	ODI/NDI	Once per applicable assessment period	✓	✓	✓	✓
	Health-related quality of life	EQ-5D-5L	Once per applicable assessment period	✓	✓	✓	✓
	Impression of change	PGIC	Once per applicable assessment period	—	✓	✓	✓
	Sleep, activity patterns and RR-intervals	Actigraphy subset	Continuous recording for seven consecutive days in the subset	✓	✓	✓	✓
	Holistic responder status	Composite measure	Derived after completion of data collection using outcomes obtained at each follow-up assessment	—	✓	✓	✓
	Pain catastrophizing	PCS	Once per applicable assessment period	✓	✓	✓	✓
	Anxiety and depression	HADS	Once per applicable assessment period	✓	✓	✓	✓
	Work status	Self-developed questionnaire	Once per applicable assessment period	✓	—	✓	✓
	Patient expectations and fulfilment	Open question	After last assessment period	✓	—	—	✓
	Patient unwanted stimulation awareness	Self-developed questionnaire	Once per applicable assessment period	—	✓	✓	✓
	Time spent in body postures	IPG output	Extracted at visits for the preceding follow-up interval	—	✓	✓	✓
Safety	Adverse events and serious adverse events	Physician reporting	Recorded continuously and reviewed at each follow-up	—	✓	✓	✓
Feasibility	Proportion of successful DTM SCS trials	Investigator/device reporting		—	✓	✓	✓
	Technical IPG details, including ECAP-related data	IPG output	Extracted at visits for the preceding follow-up interval	—	✓	✓	✓
	DTM SCS stimulation parameters	IPG output	Extracted at visits for the preceding follow-up interval	—	✓	✓	✓
	Battery consumption/recharge frequency	IPG output	Extracted at visits for the preceding follow-up interval	—	✓	✓	✓

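### Read literally, the main incremental QALY can be computed only for patients with a 12-month EQ-5D-5L, and it discards partial follow-up that the planned mixed model would use

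*Protocol article*

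**What the plan says.** All of the following is in the protocol article.

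- **Estimator (section 3.7, Data analysis).** "Patient-level quality-adjusted life-years (QALYs) will be calculated using EQ-5D-5L index scores". The method is area under the curve, in which "utility values are linearly interpolated over the study period and the resulting areas are summed".
- **Comparator (section 3.7).** "A second QALY estimate will be calculated by extrapolating the baseline EQ-5D-5L index value over 12 months". The incremental QALY is obtained by "subtracting the baseline-extrapolated QALY from the QALY observed during DTM SCS over the 12-month follow-up period".
- **Schedule (section 3.4.1, Table 1).** EQ-5D-5L is collected at baseline (V0), 1 month (V1), 6 months (V2) and 12 months (V3).
- **Missing data (section 3.7).** "Main analyses will be performed using the data as observed". The next sentence adds: "Sensitivity analyses will be conducted to assess the robustness of the findings in relation to the handling of missing data".
- **Model for repeated outcomes (section 3.7).** "Longitudinal mixed models will be used for continuous repeated outcomes".
- **Retention (sections 3.3 and 3.4.3).** Follow-up continues after a switch away from DTM SCS. Patients who miss a visit are telephoned, and whatever can be done remotely is collected if they agree.

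**The concern.** Analysing data as observed is sound for a likelihood-based mixed model. Every available visit is used, and the estimate remains valid when dropout depends on values already observed. That protection is lost when each patient is first reduced to a single derived number that needs a value at the end of the horizon. A patient with baseline, V1 and V2 but no V3 has no 12-month area on observed data, and so has neither a QALY nor an incremental QALY.

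Two things follow. The same questionnaire would be analysed on two different sets of patients: all available visits in the mixed model, and only patients with V3 in the QALY. And if a missing V3 is related to earlier response, the QALY gain is biased, upward if those who did poorly are the ones missing. The cohort has no control group, so there is no comparator in which such a bias could partly cancel. If a missing V3 is unrelated to response, only precision is lost.

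**Working it through.** The article states no QALY figure, utility value or dropout rate, so there is no figure to reproduce. The check has three parts.

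**1. What the area needs.** Put baseline at time 0 and the visits at 1, 6 and 12 months, in years: 0, 1/12, 6/12, 1. The trapezoid weights are:
- baseline: (1/12)/2 = 0.042
- V1: (6/12 − 0)/2 = 0.250
- V2: (1 − 1/12)/2 = 0.458
- V3: (1 − 6/12)/2 = 0.250

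They sum to 1. Incremental QALY = 0.042·u0 + 0.250·u1 + 0.458·u6 + 0.250·u12 − u0.

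Take an assumed patient with utilities 0.35, 0.55, 0.60, 0.60:
- All four values: 0.0146 + 0.1375 + 0.2750 + 0.1500 − 0.35 = 0.227.
- V2 missing, bridged from V1 to V3: (0.35 + 0.55)/2 × 1/12 + (0.55 + 0.60)/2 × 11/12 − 0.35 = 0.215. It can still be computed.
- V3 missing: the 6-to-12-month segment, half the horizon, has no right-hand end. Stopping at 6 months gives an area of 0.277. Subtracting the 12-month baseline QALY gives 0.277 − 0.350 = −0.073 for a patient who improved, which is meaningless.

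So baseline and V3 are indispensable, and V1 and V2 are not.

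**2. Simple illustration (all inputs assumed).** Patients with V3 follow the profile above, with a gain of 0.227. The all-patient mean is (1 − d) × 0.227 + d × (gain in those without V3), where d is the proportion without V3. Of 200 patients, 180, 160 or 140 would have a QALY at d = 10%, 20% or 30%.

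| Patients without V3 | Their gain | All-patient mean at d = 10%, 20%, 30% | Overstatement |
|---|---|---|---|
| Same course | 0.227 | 0.227, 0.227, 0.227 | 0% |
| Half the gain at 6 and 12 months | 0.139 | 0.218, 0.209, 0.201 | 4%, 8%, 13% |
| Back at baseline by month 6 | 0.050 | 0.209, 0.192, 0.174 | 8%, 18%, 30% |

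**3. Simulation (all inputs assumed).** Utilities are multivariate normal: baseline mean 0.40, SD 0.25, correlation 0.4 with baseline and 0.6 between follow-ups, constant gain g from month 1. The true incremental QALY is then g × (0.250 + 0.458 + 0.250) = 0.958·g. V3 is deleted with a probability that depends only on the observed change from baseline to V2. The odds ratio (OR) is per SD worse change.

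| Gain g | V3 missing | OR | True | Patients with V3 | Overstatement |
|---|---|---|---|---|---|
| 0.25 | 5% | 1.5 | 0.239 | 0.244 | +2% |
| 0.15 | 5% | 1.5 | 0.144 | 0.148 | +3% |
| 0.20 | 10% | 2 | 0.191 | 0.206 | +7% |
| 0.25 | 15% | 2 | 0.240 | 0.261 | +9% |
| 0.15 | 15% | 2 | 0.144 | 0.165 | +15% |
| 0.10 | 20% | 2 | 0.096 | 0.124 | +29% |
| 0.10 | 25% | 3 | 0.096 | 0.145 | about +50% |

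With SD 0.20 and correlations 0.6 and 0.7, the case g = 0.15, 15% missing, OR 2 falls to +9%. With OR 1 there is no bias. Under this mechanism the area under visit means, with the V3 mean estimated from baseline, V1 and V2, stays within about 0.1% of the true value.

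**The case against.** **The exclusion is inferred.** No sentence says that patients without a 12-month EQ-5D-5L are dropped. The as-observed sentence closes the paragraph on secondary outcomes and is not tied to the QALY, and a per-patient QALY is compatible with imputing utilities first. This stands, and it is why the point is limited to the literal reading. Against it, the sentence covers main analyses without restriction, EQ-5D-5L is a secondary outcome, and nothing exempts the QALY derived from it.

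**This is detail for an analysis plan.** The absence of a QALY-specific missing-value rule in a journal article is no fault in itself, and a plan that is not shown may contain one. The point is narrower: the article does fix the estimator and the basis for the main analyses, and together these discard data that its own mixed model would use.

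**The problem is already mitigated.** Follow-up after switching, telephone contact and a web-based questionnaire all act against poor responders lacking V3, and sensitivity analyses on missing data are planned. This also stands. These provisions reduce the problem, but they do not change the main estimate.

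**The size is assumed and the stakes are modest.** Every input to the illustrations is assumed. The absolute bias in the case with 15% missing and OR 2 is about 0.021 whatever the gain, so small assumed gains inflate the percentage. The QALY is not listed as an outcome in its own right in section 3.4, and the baseline-held comparator is itself a strong assumption.

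**A stronger reading is tempting.** A reader might infer that the reported gain is known to be a gain in those who completed treatment, and known to be too high. The documents support neither. The restriction is to patients with baseline and V3, whether or not they skipped other visits or left DTM SCS, and neither the direction nor the size of any bias can be derived from the article.

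**Conclusion.** The point holds in its conditional form. Unless a rule elsewhere says otherwise, an interpolated patient-level 12-month QALY on data as observed yields a main incremental QALY only for patients with both a baseline and a 12-month EQ-5D-5L. That part is arithmetic and needs no assumption beyond the visit schedule.

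Whether the result is biased depends on why V3 is missing. Bias is zero if missingness is unrelated to response. If poor responders are the ones missing, it is upward: about +2% to +15% under mild to moderate assumptions, and about +50% only with 25% missing, strong dependence and a small gain. These figures show what could happen and are not predictions for this cohort. The change is worth making because a better estimator is already within the plan and uses data already collected.

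**What to change.** Make the main incremental QALY the area under the EQ-5D-5L visit means from the longitudinal mixed model already planned. It is a linear combination of the four means, −0.958·m0 + 0.250·m1 + 0.458·m6 + 0.250·m12, where −0.958 = 0.042 − 1, and the confidence interval comes from the same model. Every patient with a baseline and any follow-up EQ-5D-5L contributes. An equivalent choice is multiple imputation of missing visit utilities before the patient-level area is computed. In either case, value utility at 0 from the date of any death. Report the patient-level area in those with an observed V3 as a labelled sensitivity analysis, with the number contributing.

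The cost is a sentence or two in the analysis plan and one contrast from a planned model, with no new data or patients. Analyses start only after follow-up is complete, so the rule can still be set in advance. The downsides are reliance on missing at random, as in the other mixed models, and a reported gain that may be smaller.

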### Data monitoring and oversight

3.8

The trial management group, consisting of [name] and [name], will act as the main decision-making and steering body of the project. A kick-off meeting was organised at the start of the study to establish common working procedures across participating centres. The responsibilities of the trial management group include agreeing on study procedures and management policies, monitoring overall study progress and deliverables, and deciding on major changes to the work programme.

Principal investigators at each recruiting centre will be responsible for patient recruitment and data collection at their own site. The study coordinator at Vrije Universiteit Brussel will regularly review entered data for completeness and consistency and will coordinate data queries when needed. Statistical analyses will be conducted by the project biostatistician using pseudonymised datasets and according to the prespecified statistical analysis strategy. The trial management group will additionally oversee scientific communication, dissemination of study results and exploitation of project outputs. The funder will not have authority to modify the analysis, interpretation or publication of the study findings.

## Anticipated results

4

ENDLESS is expected to provide pragmatic longitudinal evidence on the feasibility, effectiveness and safety of open-loop and closed-loop DTM SCS in patients with PSPS-T2 across European clinical practice. The study will generate data on pain trajectories, patient-reported outcomes, medication use, work participation, unwanted stimulation awareness, technical programming parameters, ECAP-related information, battery performance and safety events over 12 months. By combining repeated patient-reported assessments with device-derived data, ENDLESS will provide insight into how DTM SCS is delivered, optimized and experienced in routine care. The planned trajectory analyses may also identify clinically relevant response patterns within this heterogeneous patient population.

## Discussion

5

This protocol describes a pragmatic European cohort study designed to evaluate open-loop and closed-loop DTM SCS in patients with PSPS-T2. The main strength of ENDLESS is its combination of standardized follow-up, ecological momentary assessment, validated patient-reported outcomes and device-derived technical data across multiple countries and clinical settings. This design will allow evaluation of both clinical outcomes and real-world feasibility, including programming characteristics, ECAP-informed delivery, battery performance and patient unwanted stimulation awareness.

The observational design also introduces limitations. As patients will not be randomized and treatment will be delivered according to local clinical practice, causal conclusions regarding comparative effectiveness between open-loop and closed-loop DTM SCS will be limited. The absence of a control group or sham-stimulation condition is an additional limitation. Pain and other patient-reported outcomes may be influenced by expectations, clinical attention, regression to the mean, natural symptom fluctuations and other contextual components of care. Consequently, observed changes cannot be attributed exclusively to the physiological effects of DTM SCS. The study should therefore be interpreted as an evaluation of real-world clinical outcomes and implementation rather than as a controlled assessment of stimulation-specific efficacy. Randomised and, where methodologically and ethically feasible, sham-controlled studies remain necessary to establish causal treatment effects and comparative efficacy. In addition, country-specific reimbursement rules, trial procedures and follow-up pathways may influence treatment implementation and outcomes. Nevertheless, these differences are also clinically relevant, as they reflect the context in which SCS is delivered in routine European practice. ENDLESS is therefore expected to complement existing randomized and national cohort evidence by documenting the implementation, feasibility and patient-centred outcomes of DTM SCS in a real-world PSPS-T2 population.

